#### 2.11.2. Secondary Outcome

The secondary outcome will be assessed by changes in the HB-M score from baseline to 16 weeks, changes in the CSEI-S, PHQ-15, SRI, BDI, STAXI, and STAI from baseline to 8 and 16 weeks, and changes in the fNIRS and HRV from baseline to 8 weeks.

CSEI-S measures the core emotions of the patient in a clinical setting [38]. PHQ-15 assesses depression and physical symptoms [39]. SRI measures the degree of stress response [40]. BDI measures the current severity of depression, regardless of psychiatric diagnosis [41]. STAXI measures anger experiences and forms of anger expression [42]. STAI measures state anxiety and trait anxiety [43]. fNIRS shows prefrontal cortex activation which is prominent during both emotional processing and regulation [44]. HRV measures heart rate variability consistent with autonomic nervous system functional status [45].

We will use ANCOVA or baseline-variables-corrected multiple regression analysis for the efficacy assessment of the CSEI-S, PHQ-15, SRI, BDI, STAXI, STAI, fNIRS, and HRV variables. The baseline score will be used as a covariate, in which case a PP analysis will be performed without handling missing values.

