## Abstract

Background: Hwa-Byung is a culturally bound syndrome prevalent in Korea, characterized by intense emotional distress and physical symptoms related to suppressed anger. Patients frequently report experiencing chest tightness, heat sensations, and globus pharyngeus (the sensation of a lump in the throat). These physical symptoms often accompany psychological distress and can exacerbate the sense of frustration and helplessness associated with the condition. The distinctive presentation of these symptoms highlights the necessity for therapeutic interventions that address both the emotional and physical aspects of Hwa-Byung. Conventional therapeutic methods, such as Emotion-to-Emotion Therapy (ETE), have shown efficacy in treating this condition. This study aims to assess the efficacy of Virtual Reality-based Emotion-to-Emotion Therapy (VR-based ETE) compared to conventional ETE, utilizing immersive digital platforms to enhance therapeutic engagement. Methods: This single-center, randomized, assessor-blind, parallel-group clinical trial will enroll 96 participants, evenly divided into two experimental groups and one control group. Over eight weeks, each participant will undergo 12 intervention sessions. Experimental group 1 will receive conventional ETE, experimental group 2 will receive VR-based ETE, and the control group will receive Hwa-Byung management training materials. The primary outcome will be the change in symptoms, measured by the Likert Scale for Major Symptoms of Hwa-Byung from baseline to 8 weeks. Secondary outcomes will include psychometric scales and physiological measures such as the core seven-emotions inventory short form, physical health questionnaire, stress response index, Beck depression inventory, state-trait anger expression inventory, state-trait anxiety inventory, functional near-infrared spectroscopy, and heart rate variability. For economic efficiency assessment, quality-adjusted life-years will be the primary outcome using the EuroQol-5 dimension, and the secondary outcome will be using the EuroQol visual analog scale. Discussion: ETE is a recognized oriental psychotherapy that enhances symptom management, self-regulation, and stress coping. VR is expected to deepen treatment immersion. By combining these strengths, VR-ETE may further improve emotion regulation and alleviate psychosomatic symptoms. If successful, this study will not only advance the treatment of Hwa-Byung but also contribute to the modernization of traditional Korean medicine through the integration of digital therapies.

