### 2.5. Interventions

The ETE group (experimental group 1) and VR-based ETE group (experimental group 2) will receive ETE two times per week for the first four weeks and once a week for the next four weeks (a total of 12 times). The daily management group (control group) will receive Hwa-Byung management training materials and wait for eight weeks living a daily life. Hwa-Byung management training materials will be the same for the experimental and control groups.

ETE will be performed by a specialist in oriental neuropsychiatry or a resident who has been educated by a specialist in oriental neuropsychiatry and has over one year of clinical experience in neuropsychiatry of traditional Korean medicine.

We will follow the ETE protocol [17]. It consists of five stages: (1) assessment of emotion and physical symptoms (CSEI-S, Mentalizing the Room of Mind (MRM), SUDS); (2) analyze the relationship between emotion and physical symptoms, analyzing emotion and sensation with oriental neuropsychiatric perspective, and finding core emotion; (3) training—depending on the patient’s emotional state, choose from exposure mindfulness meditation, breathing meditation, somatic mindfulness meditation, upper danjeon meditation, joy meditation, lower danjeon meditation, middle danjeon meditation, resource mindfulness meditation, and integrated-triple danjeon meditation; (4) assessment of emotion and physical symptoms after intervention (CSEI-S, MRM, SUDS); and (5) managing emotion education.

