### 2.9. Compliance Assessment

Compliance assessment will be performed as follows:$$Compliance\left(\%\right)=\frac{Number\;of\;performed\;interventions}{Number\;of\;planned\;interventions}\times 100$$

Compliance (%) during the trial should be at least 75%. If the compliance (%) of the subjects is less than 75%, it is considered poor and is excluded from the Per-Protocol (PP) analysis.

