### 2.10. Statistical Analysis

Efficacy analysis will be evaluated primarily based on the Full Analysis Set (FAS) principle and secondarily according to the Per-Protocol (PP) principle of the primary outcome. Missing values will be imputed appropriately according to why they occur. Subjects are excluded from FAS analysis in following cases: failure to meet eligible criteria, no intervention specified in the clinical study plan has been received, no data have been collected because they have never been evaluated since randomization. Subjects will be excluded from the per-protocol (PP) analysis if they meet any of the following conditions: 1. Dropped out during the trial. 2. Violated the inclusion or exclusion criteria. 3. Had less than 75% compliance with the overall intervention. Additionally, other serious violations of the study protocol may also be considered as grounds for exclusion from the PP analysis. The demographic data of the study subjects included in this trial and baseline clinical history data will be presented with mean and standard deviation (SD) for continuous data for each group and frequency and percentage for categorical data. For each group, an independent sample t-test or Wilcoxon rank sum test will be performed depending on normality in the case of continuous variables, and for categorical variables, a Pearson chi-square test or Fisher’s practice test will be performed.

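### Eight secondary measures are assigned only a per-protocol analysis without missing-data handling, and the 75% attendance rule behind that set can exclude patients only in the two active arms

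*Protocol article*

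**What the plan says.** - **General rule (section 2.10).** The main basis is stated as "Efficacy analysis will be evaluated primarily based on the Full Analysis Set (FAS) principle". The PP analysis ranks after it and is worded as "secondarily according to the Per-Protocol (PP) principle of the primary outcome". The same section says that missing values will be imputed according to why they arose.
- **Secondary outcomes (section 2.11.2).** ANCOVA or adjusted multiple regression is planned "for the efficacy assessment of the CSEI-S, PHQ-15, SRI, BDI, STAXI, STAI, fNIRS, and HRV variables". The baseline score is the covariate, "in which case a PP analysis will be performed without handling missing values". No other analysis set is named for these measures. Week-16 HB-M is also secondary ("The secondary outcome will be assessed by changes in the HB-M score from baseline to 16 weeks") but does not appear in that analysis sentence.
- **PP set (sections 2.9 and 2.10).** PP leaves out dropouts, eligibility violators, possibly other serious violators, and poor compliers. Compliance is interventions performed divided by interventions planned: "If the compliance (%) of the subjects is less than 75%, it is considered poor and is excluded from the Per-Protocol (PP) analysis".
- **Planned interventions (section 2.5).** The ETE and VR-based ETE arms have 12 sessions each. The control arm "will receive Hwa-Byung management training materials and wait for eight weeks living a daily life".

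**The concern.** An analysis by randomised arm keeps the arms comparable. A PP analysis gives this up in any trial, which is why it normally serves as a sensitivity analysis. Here it is the only analysis named for all the psychometric and physiological secondary measures other than HB-M.

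Two features make it worse. First, one of the PP exclusions depends on attending treatment sessions, and only two of the three arms have sessions. A contrast with control then sets patients filtered on attendance against patients who were not filtered that way. Second, results already measured in excluded patients are set aside. Section 2.2 allows efficacy tests in subjects who drop out, and a patient with 8 sessions may still attend the week-8 and week-16 assessments.

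At stake is whether a difference from control on these measures can be read as an effect of treatment. ETE versus VR-ETE share the same attendance rule, but that comparison too is made in a set selected after randomisation.

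**Working it through.** The plan gives no power or precision figure for these eight measures, so there is none to reproduce. The check compares sections and does a little arithmetic.

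**1. Which analysis set applies?** Section 2.10 can be read in two ways.
- If its opening covers all efficacy, FAS with imputation is the main analysis of the eight measures. Section 2.11.2 then contradicts it on both the set and the missing data.
- If its reference to the primary outcome limits the rule to HB-M at week 8, the sections agree, but the eight measures have no FAS analysis.

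Either way the text needs correcting. By contrast, section 2.11.1 gives the primary outcome an FAS analysis with imputation, and section 2.13 puts FAS first for the economic endpoints.

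**2. What the 75% rule does in each arm** (sections 2.5 and 2.9).

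| Arm | Planned sessions | Minimum for PP | Can the rule exclude? |
|---|---|---|---|
| ETE | 12 | 0.75 × 12 = 9 | Yes, at 8 or fewer |
| VR-based ETE | 12 | 0.75 × 12 = 9 | Yes, at 8 or fewer |
| Control | none | undefined, or met automatically if handing over the materials counts | No |

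**3. How large the PP set can be** (section 2.4.3). With 32 per arm and the protocol's own 25% dropout, 32 × 0.75 = 24 per arm, or 72 of 96. This applies to all arms. Attendance exclusions come on top, in the active arms only.

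**4. How much bias could follow?** The documents give neither the share of patients below 9 sessions nor the relation of attendance to outcome. The following is an illustration under assumptions that are not in the documents:
- there is no true effect;
- all 32 controls are retained;
- a fraction f of 10% to 25% of an active arm is removed for low attendance;
- latent attendance and outcome are jointly normal with correlation ρ of 0.2 to 0.5.

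The retained active mean shifts by ρ × φ(z_f)/(1 − f) standard deviations, where φ is the normal density and z_f the f-quantile.
- f = 0.10, ρ = 0.2: 0.2 × 0.1755/0.90 = 0.04 SD.
- f = 0.25, ρ = 0.5: 0.5 × 0.3178/0.75 = 0.21 SD.
- ρ = 0: no shift.

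A simulation of the same set-up agrees. With 29 and 24 active patients retained respectively, a nominal 5% two-sided test rejects in about 5.3% and 13% of trials.

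**The case against.** The case on the other side is that these are supportive outcomes, that the primary outcome has its own FAS analysis, and that section 2.11.2 never says PP is the sole analysis. All three are true. They limit the consequences, but no FAS analysis of the eight measures is named, and the instruction not to handle missing values is explicit.

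Several stronger readings are tempting, and the documents do not support them.

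- **That every secondary endpoint is affected.** Week-16 HB-M is outside the PP sentence, so its analysis set is open, and the economic endpoints are FAS-first.
- **That controls are unselected.** Dropout, eligibility and serious-violation exclusions apply to them too. Only the attendance criterion falls on one side.
- **That the bias favours the active arms.** Dropping poor attenders may do so. But section 2.6.2 withdraws anyone who starts a new treatment. If symptomatic controls seek care and leave, the remaining controls look better, and the bias runs the other way.
- **That PP makes standard errors about 15% larger.** That figure, √(96/72) = 1.155, compares everyone enrolled with those left after dropout. Most dropouts would lack outcomes under any analysis set. The loss due to PP itself is the patients who were measured but excluded, and their number is unknown.
- **That the abstract gives controls sessions.** It says "each participant will undergo 12 intervention sessions", but it also assigns the control group only training materials. This is loose wording and carries no weight here.

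One caution about the remedy stands. The FAS in section 2.10 itself leaves out subjects who received no intervention, which could also fall unevenly across arms.

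**Conclusion.** The point holds for the eight named measures. Section 2.11.2 gives them only a PP analysis without missing-data handling, which either conflicts with section 2.10 or leaves them without an FAS analysis. The attendance criterion can remove ETE and VR-ETE patients but no control, so contrasts with control are selected differently by arm after randomisation, and some measured outcomes are not used.

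The size and direction of any bias cannot be computed from the documents. The range of 0.04 to 0.21 SD rests wholly on the assumed exclusion rates and correlations and is not an estimate for this trial. Bias is absent only if attendance and dropout are unrelated to outcome, and the plan gives no reason to expect that.

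The primary FAS analysis of HB-M at week 8 is not affected. Its secondary PP analysis uses the same compliance rule and so has the same gap for controls.

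**What to change.** - In section 2.11.2, make FAS the main analysis for the eight measures, by randomised arm and with all available post-baseline data. State the missing-data method, for example baseline-adjusted ANCOVA with multiple imputation. A mixed model is an alternative for the six scales measured at both weeks 8 and 16.
- State the same for week-16 HB-M, and word section 2.10 so that it clearly covers secondary outcomes.
- Say how the FAS exclusion for having received no intervention applies in the control arm.
- Keep PP as a sensitivity analysis only. Either define a PP criterion that controls can meet or fail, or do not apply the attendance rule in comparisons with control.

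The cost is a change of wording and slightly more analysis, with no new data. Estimates may turn out less favourable to the active arms. The change should be made before the data are analysed.

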### 2.12. Safety Assessment

Changes in laboratory test results before and after the trial will be clinically evaluated. All adverse events during the trial will be listed with a detailed descriptive explanation. Data will be collected through patient self-reporting and researcher observation. The frequency of adverse events related to and unrelated to interventions will be recorded and presented as descriptive statistics. A list of adverse reactions, including frequency, expression rate, definite occurrence time, occurrence rate, severity, and intervention casualty, will be presented with graphs, if necessary. If statistical analysis is required, the paired t-test, McNemar test, analysis of variance [ANOVA], t-test, chi-square test, and/or Fisher’s exact test will be performed according to the characteristics of the variables and the purpose of the statistical evaluation.

### 2.13. Economic Efficiency Assessment

An economic evaluation alongside clinical trial will be performed to check the cost effectiveness among the interventions in this trial. The primary economic endpoint will be assessed using the cost per Quality-Adjusted Life-Year (QALY). The estimation of quality of life for the QALY calculation will use the quality-of-life derived EQ-5D as the main evaluation variable, and the calculation will use the area under the curve method [46]. The costs will be calculated by combining the number of treatments and cost units. The secondary economic endpoint will be assessed using effectiveness evaluation indicators such as cost per EQ-VAS calculated with EQ-VAS.

The economic analysis will be primarily evaluated based on the FAS principle and secondarily based on the PP principle to check the sensitivity of the missingness. Missing values will be imputed properly based on analysis of mechanism in the same manner as in the efficacy analysis. The first analysis period is 18 weeks (total follow-up period), and if an estimation of the subsequent period is necessary, the second analysis will be estimated by extrapolating the cost and effect after the tracking period through a regression model, or by performing decision modeling analysis. If the total analysis period (time horizon) is extrapolated after the clinical study period, the cost unit will be settled to the Korean currency unit (KRW) in 2021, and a 5% discount rate will be applied based on the economic evaluation guidelines of the Health Insurance Review and Assessment Service.

The analytical perspective of this study is a social perspective. In the baseline analysis, the representative values (such as average) of parameters will be used, and in the sensitivity analysis, probabilistic sensitivity analysis will be performed through the distribution and representative values of all possible estimated parameters.

The results will be presented in tables including the incremental cost-effectiveness ratio, cost-effectiveness plane, Cost-Effectiveness Acceptability Curve (CEAC), and value of information analysis graph. The cost-effectiveness plane will include a confidence interval confirmed by non-parametric methods. The CEAC will confirm the sensitivity of cost effectiveness according to changes in national threshold. The value of the information analysis graph will estimate the value of the information of the target population group.

When the number of samples in this study is less than 30, the statistical analysis will be performed after verifying the normality of all continuous variables through the Shapiro–Wilk test and the statistical significance level will be tested with a 0.05 *p*-value. The analysis programs are Stata (MP 16.1 Version) and R (4.3.2 Version), and extrapolation through modeling is performed using Treeage Pro (Healthcare Version 2023).

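### The per-protocol economic analysis is meant to test sensitivity to missing data, but it mixes dropout with compliance and never varies the missing-data assumption

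*Protocol article*

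**What the plan says.** Section 2.13 has the economic analysis evaluated primarily in the FAS and "secondarily based on the PP principle to check the sensitivity of the missingness". On the missing values themselves it says "Missing values will be imputed properly based on analysis of mechanism in the same manner as in the efficacy analysis".

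The sets are defined in Section 2.10. PP excludes a participant who meets any of these conditions: "1. Dropped out during the trial. 2. Violated the inclusion or exclusion criteria. 3. Had less than 75% compliance with the overall intervention". It adds that "other serious violations of the study protocol may also be considered as grounds for exclusion from the PP analysis". Section 2.9 repeats the attendance rule: "If the compliance (%) of the subjects is less than 75%, it is considered poor and is excluded from the Per-Protocol (PP) analysis". For the FAS, Section 2.10 begins its exclusions thus: "Subjects are excluded from FAS analysis in following cases: failure to meet eligible criteria". It then also removes participants who received no intervention or were never assessed after randomisation.

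Three other places bear on the point. Section 2.5 gives each therapy arm 12 sessions and the control arm training materials only. Section 2.13 builds cost from the number of treatments and unit costs. Section 2.4.3 allows for 25% dropout.

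**The concern.** Section 2.13 asks whether the cost-utility result depends on how missing data are treated. To answer that, the assumption about the unseen values has to change while the population stays the same. The planned comparison does the reverse: it changes the population and leaves the assumption alone.

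Two misreadings can follow. A difference between FAS and PP caused by poor attendance could be put down to missing data. Agreement between them could be reported as robustness to missing data when it shows nothing of the kind.

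Cost-effectiveness is one of the study's stated aims, and cost per QALY is the primary economic endpoint. The QALY is an area under EQ-5D values collected at visits 1, 8, 12 and 13, so a participant who leaves early loses part of it. The protocol's own rules make informative dropout plausible: starting a new treatment leads to withdrawal (Section 2.6.2), and dissatisfaction is a listed reason to leave (Section 2.8.2). Either could remove poor responders selectively.

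**Working it through.** The plan gives no figure to reproduce here. The check compares the two set definitions and then shows with assumed numbers what the comparison can and cannot detect.

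**1. The sets side by side (Sections 2.9 and 2.10)**

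| Criterion | FAS | PP | Differs? |
|---|---|---|---|
| Fails eligibility | out | out | no |
| No intervention, or never assessed after randomisation | out | out if counted as a dropout or non-complier | little or none |
| Dropped out, some data | in, imputed | out | yes |
| Compliance below 75%, complete data | in | out | yes |
| Other serious violation | in | may be out | yes |

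Only the third row concerns missing data. The compliance cut-off is 0.75 × 12 = 9 sessions, so someone with 8 sessions and every EQ-5D and cost value recorded leaves PP. Controls have no sessions, so this rule acts on the therapy arms only. Because cost counts treatments, removing low attenders raises mean therapy-arm cost mechanically. Between the two therapy arms the shift depends on how their attendance differs.

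**2. Why agreement can be uninformative**

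Suppose one arm has n₁ observed participants with mean m and n₀ dropouts imputed at the observed mean. The FAS mean is (n₁m + n₀m)/(n₁ + n₀) = m, which is also the completers' mean. If nobody is excluded for compliance, FAS equals PP whatever the dropouts' true values are. Imputation from observed covariates (missing at random, MAR) behaves in much the same way when those covariates do not explain the dropouts' poorer outcome.

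**3. Illustration with QALYs and cost**

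All inputs are assumed: 400,000 simulated participants per arm, one therapy arm against control, a linear utility path over 16 weeks, a mean utility gain 0.10 larger on therapy, and one cost unit per session. The expected incremental QALY is 0.10 × (16/52)/2 = 0.0154.

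- *Scenario A:* nothing missing; about 21% of the therapy arm attend 4 to 8 sessions, more often the poor responders.
- *Scenario B:* full attendance; about 27% of the therapy arm drop out because of unobserved poor response, 10% of controls drop out at random, and values are imputed at the observed arm mean.

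| Scenario | Analysis | Incremental QALY | Incremental sessions | Sessions per QALY |
|---|---|---|---|---|
| A | truth and FAS | 0.01545 | 10.77 | 697 |
| A | PP | 0.01764 | 12.00 | 680 |
| B | truth | 0.01536 | 12.00 | 781 |
| B | FAS and PP | 0.01902 | 12.00 | 631 |

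In A, PP moves QALYs by 0.01764/0.01545 − 1 = 14% and sessions by 12.00/10.77 − 1 = 11%. The ratio moves by 680/697 − 1 = −2%, because numerator and denominator rise together. In B, FAS and PP do not differ, yet both overstate QALYs by 0.01902/0.01536 − 1 = 24% and understate the ratio by 1 − 631/781 = 19%.

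**4. Both problems crossed (utility difference only)**

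Assumed: benefit e = 0.06; utility SD 0.15; a fraction c of the therapy arm complies poorly and gains nothing; dropout p = 25% (the allowance in Section 2.4.3); informative dropouts in the therapy arm lie δ = 0.5 × 0.15 = 0.075 below what the imputation predicts. Then FAS = e(1 − c), PP = e and truth = e(1 − c) − pδ, where pδ = 0.25 × 0.075 = 0.019.

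| Situation | FAS | PP | Truth | PP − FAS | FAS − truth |
|---|---|---|---|---|---|
| Nothing missing, c = 20% | 0.048 | 0.060 | 0.048 | 0.012 | 0 |
| Random dropout, c = 20% | 0.048 | 0.060 | 0.048 | 0.012 | 0 |
| Informative dropout, c = 0 | 0.060 | 0.060 | 0.041 | 0 | 0.019 |
| Informative dropout, c = 20% | 0.048 | 0.060 | 0.029 | 0.012 | 0.019 |

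Simulated trials of 32 per arm with regression imputation gave means within 0.003 of these values. Under these assumptions the PP − FAS gap follows compliance, and the bias from missing data follows something the gap does not register.

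**The case against.** The strongest reply has four parts.

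- *Dropout is itself a PP exclusion, so the contrast does touch missingness.* True: it sets dropouts imputed against dropouts removed. But that is combined with the compliance rule, and removing dropouts offers no alternative assumption about their unseen values.
- *No imputation method is fixed.* True: the protocol says it will follow the diagnosed mechanism. If the FAS imputation allowed for informative dropout, FAS and PP could differ for that reason. Step 2 therefore depends on MAR-type imputation. Observed data alone cannot tell MAR from informative dropout, so diagnosing the mechanism does not replace varying the assumption.
- *The SAP may hold a proper check.* It may, and the absence of imputation detail from an article is not the point here. The point is the stated purpose of the PP analysis, which its definition cannot serve. The other sensitivity analyses named in Section 2.13 vary something else: the probabilistic analysis varies parameters, and the acceptability curve varies the threshold.
- *The false alarm is weak for the ratio.* This stands: about 2% in Scenario A. Incremental QALY and incremental cost, which place the result on the cost-effectiveness plane, moved by 14% and 11%.

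A reader might also infer that the two sets differ in eligibility. They do not, because Section 2.10 removes eligibility failures from both.

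**Conclusion.** The point holds in limited form. The PP economic analysis cannot do the job Section 2.13 gives it: against FAS it mixes dropout with compliance below 75% and possibly other serious violations, and it leaves the missing-data assumption unchanged. The two can differ with nothing missing. If the FAS imputation is MAR-type, they can also agree while informative dropout biases both.

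Two stronger readings go too far. One is that agreement between FAS and PP is to be expected under informative dropout. That needs MAR-type imputation and few compliance exclusions; with both problems present (last row of step 4) the two differ. The other is that the cost per QALY in this trial is biased by a known amount. The 24% and 19% come from assumed effects, dropout models and imputation; they show that the mechanism works, and the document supplies no basis for a trial-specific figure.

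The FAS remains the primary economic set, and no efficacy result is affected. The change is worth making because a robustness statement about the primary economic endpoint would otherwise rest on the wrong comparison.

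**What to change.** In Section 2.13, separate the two purposes, for example:

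*The economic analysis will be carried out in the FAS. A PP analysis will be reported as an adherence analysis, and no conclusion about missing data will be drawn from it. Sensitivity to missing data will be examined within the FAS by repeating the imputation with the imputed EQ-5D values of dropouts lowered, and their imputed costs raised, by a prespecified range of shifts. Shifts will be applied by arm: in the therapy arms alone and in all arms.*

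Report the incremental QALY, incremental cost, ICER and acceptability curve at each shift, with zero shift as the reference, and the shift at which the conclusion changes. Set the range before outcome data are seen. The details can sit in the SAP, but the purpose given to PP should be corrected wherever it is stated.

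The cost is a change of wording and a few extra runs of the imputation code, with no new data or participants. The downside is that the reported robustness range will probably be wider than an FAS–PP comparison would show.

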# DJ-E-ZZZ [DJ: Daejeon Korean Medicine Hospital of Daejeon University, E: initial enrollment, ZZZ: Serial number [001, 002~]] [ex. DJ-E-014: 14th registered subjects of Daejeon Korean Medicine Hospital of Daejeon University].

Screening tests should be conducted within ten days prior to visit 1 (baseline visit) and visit 13 should be conducted within 16 weeks (±7 days). At visit 1, the investigator will check the results of the screening test (including chest X-ray and laboratory tests), physical examination, and changes in medical history and concomitant medication between the screening and visit 1. The subjects will be randomly assigned to one of three groups: experimental group 1, experimental group 2, or the control group, and each subject will be provided with a unique identification code for tracking and analysis purposes. Before the intervention, subjects will complete the Likert Scale for Major Symptoms of Hwa-Byung (HB-M), The Core Seven-Emotions Inventory Short Form (CSEI-S), Patient Health Questionnaire-15 (PHQ-15), Stress Response Index (SRI), State-Trait Anxiety Inventory (STAI), State-Trait Anger Expression Inventory (STAXI), functional Near-Infrared Spectroscopy (fNIRS) (device name: NS1-H20AM), Heart Rate Variability (HRV), efficacy analysis (EQ-5D, EQ-VAS), and cost analysis. Experimental group 1 will be treated with ETE, and experimental group 2 will be treated with VR-based ETE, while the control group will receive Hwa-Byung management training materials only. At visits 1–12, the investigator will check for adverse effects and changes in medical history and concomitant drugs and patient compliance; subjects will receive ETE or VR-based ETE according to the corresponding intervention schedule at each visit. Tests and assessments will be conducted according to the following schedule: visit 8 (efficacy analysis; EQ-5D, EQ-VAS, cost analysis); visit 12 (HB-M, CSEI-S, PHQ-15, SRI, BDI, STAXI, STAI, fNIRS, HRV, efficacy assessment; EQ-5D, EQ-VAS, cost analysis, laboratory tests); and visit 13 (follow-up visit; HB-M, CSEI-S, PHQ-15, SRI, BDI, STAXI, STAI, efficacy assessment; EQ-5D, EQ-VAS, cost analysis, physical examination, adverse effects, changes in medical history and concomitant drugs).

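### The within-trial economic analysis is set at 18 weeks, described as the whole follow-up, but the last EQ-5D and cost assessment is at 16 weeks (17 at the latest)

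*Protocol article*

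**What the plan says.** Section 2.13 (Economic Efficiency Assessment) describes two analyses. For the main one it states: "The first analysis period is 18 weeks (total follow-up period". QALYs come from EQ-5D utilities, and "the calculation will use the area under the curve method". Projection of costs and effects beyond the observed period, by regression or decision modelling, belongs to a second analysis that is done only if needed.

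Section 2.2 (Study Procedure) sets the assessment times:

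- EQ-5D, EQ-VAS and costs are first collected at visit 1, before the intervention: "efficacy analysis (EQ-5D, EQ-VAS), and cost analysis".
- They are repeated at "visit 8 (efficacy analysis; EQ-5D, EQ-VAS, cost analysis" and again at visit 12.
- The last collection is at "visit 13 (follow-up visit; HB-M, CSEI-S, PHQ-15, SRI, BDI, STAXI, STAI, efficacy assessment; EQ-5D, EQ-VAS, cost analysis".
- The date of that last visit is given as "visit 13 should be conducted within 16 weeks (±7 days".

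Section 2.11.2 (Secondary Outcome) has the same end point for efficacy: "changes in the HB-M score from baseline to 16 weeks".

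**The concern.** Section 2.13 does more than choose an 18-week horizon. It says that 18 weeks is the length of follow-up, and sections 2.2 and 2.11.2 say otherwise. No section describes a visit, an EQ-5D questionnaire or cost collection at week 18.

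The horizon feeds directly into cost per QALY, the primary economic endpoint. Suppose an analyst takes 18 weeks at face value. The final stretch of the utility curve then has no measurement behind it, and the article gives no rule for filling it. One analyst might stop the area at visit 13, another might carry the last utility forward, and a third might rescale to 18 weeks. These can give different answers from the same data, so the main economic result would not be uniquely defined.

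The effect need not be neutral between arms. Section 2.5 places all 12 sessions in the first eight weeks, so a longer horizon adds no session costs, while it could add QALYs to an arm whose gain is carried forward. Section 2.13 takes a social perspective, so other costs could offset this, but none is scheduled for collection after visit 13.

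**Working it through.** **Inputs**

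- Stated economic period: 18 weeks (section 2.13).
- First EQ-5D and cost collection: visit 1, baseline (section 2.2).
- Last EQ-5D and cost collection: visit 13, at 16 weeks with a 7-day window either side (section 2.2).
- Last efficacy time point: 16 weeks from baseline (section 2.11.2).
- Screening: "Screening tests should be conducted within ten days prior to visit 1 (baseline visit" (section 2.2).

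**Can 18 weeks be reproduced?**

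| Interval | Arithmetic | Weeks | Shortfall against 18 |
|---|---|---|---|
| Visit 1 to visit 13, nominal | 16 | 16.00 | 2.00 |
| Visit 1 to visit 13, end of window | 16 + 1 | 17.00 | 1.00 |
| Screening to visit 13, nominal | 10/7 + 16 | 17.43 | 0.57 |
| Screening to visit 13, end of window | 10/7 + 16 + 1 | 18.43 | −0.43 |

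No route gives 18 exactly. The two that come near it count the screening period, which is not follow-up and comes before the first EQ-5D and cost collection.

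**Size of the overrun, if 18 weeks is read literally from baseline**

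- Nominal: 18 − 16 = 2 weeks, and 2/16 = 12.5%.
- Visit 13 at the end of its window: 18 − 17 = 1 week, and 1/17 = 5.9%.
- A visit at the early edge of the window (week 15) would leave 3 weeks for that participant.

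The largest attainable QALY total (utility 1 throughout) is 16/52 = 0.308 at 16 weeks, 17/52 = 0.327 at 17 weeks and 18/52 = 0.346 at 18 weeks.

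**Effect on incremental QALYs**

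The documents give no expected utility gain, so the following rests on assumptions. Let d be the between-arm utility gain at week 8, starting from zero at baseline.

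*Gain rises linearly to week 8, holds to week 16, and is carried forward to week 18:*

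- To week 16: (0.5 × 8 + 8) × d/52 = 12d/52.
- To week 18: 12d/52 + 2d/52 = 14d/52.
- Ratio: 14/12 = 1.167, whatever the value of d.

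| Assumed d | QALY gain to week 16 | QALY gain to week 18 |
|---|---|---|
| 0.02 | 0.00462 | 0.00538 |
| 0.05 | 0.01154 | 0.01346 |
| 0.10 | 0.02308 | 0.02692 |

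At unchanged incremental cost, cost per QALY becomes 12/14 = 0.857 of its 16-week value, about 14% lower.

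*Gain rises to week 8 and falls linearly to zero by week 16:* the area to week 16 is (0.5 × 8 + 0.5 × 8) × d/52 = 8d/52. Carrying a zero difference forward adds nothing, so the effect is zero.

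*Area stopped at visit 13:* the 18-week figure has no effect on QALYs.

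*Incremental QALYs rescaled from 16 to 18 weeks:* multiplied by 18/16 = 1.125, whatever the shape of the curve.

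**The case against.** The strongest reply is that 18 is a mislabelled number and not a planned overrun. Section 2.13 equates the period with follow-up, computes an area under collected EQ-5D values, and puts everything later into a separate analysis. Read as a whole, that describes an analysis confined to observed data. An area drawn through the scheduled assessments ends at visit 13 unless the analyst adds a step that the article does not state. The figure may be a slip for 16. It may also be rounded total participation time, since screening plus 16 weeks plus the visit window comes to 18.4 weeks. The schedule figure (Figure 2) was not visible in the text used for this check and could not be consulted.

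Much of this stands. A reader might infer that the planned QALY area runs past the data, or that cost per QALY will be biased by a definite amount. The documents support neither. The first follows only from applying 18 weeks literally. The second needs an assumed utility path, a carry-forward step and an unchanged incremental cost, none of which is in the article. If the horizon really were 18 weeks, costs would have to cover 18 weeks as well.

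The contradiction itself does not go away. Counting screening explains where the number might come from, but does not make it a valid horizon for utilities that start at visit 1. Nor is this a detail left out of a condensed article: it is one stated figure that conflicts with others.

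**Conclusion.** The 18-week period is wrong as written. It cannot be the length of follow-up when the last utility and cost assessment is at 16 weeks, or 17 with the window. Applied literally from baseline, it leaves 1 to 2 weeks without scheduled data when visit 13 is held on or after its nominal date (nominally 2 weeks, 12.5% of 16).

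The consequence for cost per QALY is conditional. It ranges from nothing to about 17% more incremental QALYs in the carry-forward scenario worked above. That 17% is one illustration, not an estimate and not an upper limit: a gain still growing at week 16 would give a larger proportion.

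The issue is confined to the economic evaluation. The primary efficacy outcome, HB-M change at 8 weeks, and the HB-M follow-up at 16 weeks are unaffected. It is more than a typographical matter only because the primary economic endpoint depends on this figure.

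**What to change.** Reconcile sections 2.2, 2.11.2 and 2.13. In section 2.13, restate the period of the first economic analysis as baseline to visit 13, nominally 16 weeks, and apply the same window to QALYs and costs. State that anything after visit 13 belongs to the second, extrapolation analysis. If an 18-week horizon was in fact intended, the article must say how the time after visit 13 is filled for utilities and costs.

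The cost is one number and one sentence. No visit, assessment or extra data collection is needed.
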